### Recruitment

#### Location Recruitment

Recreation facilitators at the nursing home will be contacted and asked for permission to run the study at their location via the location recruitment letter (Multimedia Appendix 1). Recreation facilitators will be contacted by email using a secure email specific for study purposes, in addition to informal communication methods (eg, in-person conversations) between the recreation facilitator and the study team.

#### Participant Recruitment

Participants will be recruited through a long-term care home in Southern Ontario. Recreational facilitators will assist in recruiting participants for the study. Moreover, brochures, pamphlets, and flyers (Multimedia Appendix 2) will be placed in the study location by the team, in addition to a town hall advertising the study. Potential participants will be asked 2 questions to determine eligibility: if they currently use email/texting/messaging to contact family members and if they believe a family member would be willing to respond to an email sent by them once a week (Multimedia Appendix 3). Collecting the contact information of the participants’ family members requires balancing of respect for the participants’ autonomy, along with their potential comfort with the study’s subject matter. After consenting, participants will be presented with 2 options so that the research team can contact their family members. One option will consist of the participant providing the research team with a ranked list of family members to potentially receive emails from the participant, along with their phone numbers. The other option will consist of providing the participants with an information sheet, written in layperson terms, which they can use to describe the study to the family members to ask if they would like to participate. Members of the research team will follow up after 3 days to see if the participants were able to contact their family members or to provide support to facilitate this contact. The research team will then offer to contact the family member on their behalf, and at such time will record the contact information of up to 3 family members and contact them using the telephone script (Multimedia Appendix 4). Recruitment for the study started in November 2019. We expected to enroll approximately 20 participants, 10 in each condition. We successfully enrolled 8 participants before the study was forced to halt due to the COVID-19 pandemic (Multimedia Appendix 5).

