### Outcomes

*Primary outcomes:* The primary outcomes of this study are loneliness and depression. Loneliness will be assessed using the UCLA Loneliness Scale-version 3 [43]. The scale is a 20-item measure using a 4-point Likert scale and has been validated for use with older adults [44]. Depression will be measured using the CES-D [45]; this is a 20-item scale, each with 4 response items ranked from 0 to 3 based on the frequency of symptoms associated with depression over the past week. A cut-off of over and equal to 16 has been used in multiple validation studies [46].

*Secondary outcomes*: The secondary outcomes of this study are quality of life and computer proficiency. Quality of life will be measured using the OPQOL-Brief and a 13-item Likert scale from 1 to 5. This scale has been validated in older adults [47]. Technological proficiency will be measured using the CPQ-12, a 12-item measure using a 1-5 Likert scale and has been well-studied in older adults [48].

*Feasibility outcomes:* The feasibility outcome measures of this study will include the number of participants that we are able to enroll in the study, adherence to the intervention (frequency of contact with the family and attendance to the program), and the rate of attrition [49]. We also intend to determine the challenges faced by the site and volunteers as a result of our intervention, in particular, the restrictions of having only university student volunteers as well as the restrictions of the daily schedules for the residents of the facility. These will both be determined quantitatively (eg, total number of participants, adherence) and qualitatively, where participants will be asked about their experiences with the program. We do not expect any adverse events as a result of our intervention.

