#### Primary Outcomes

The UCLA Loneliness Scale and the CES-D Scale will be analyzed using a repeated measures approach, as these measures will be collected weekly. The normality of the data will be assessed using the Shapiro-Wilk test; if the data are nonparametric, a Q-Q plot will be performed to identify skewness of the data. A Brown-Forsythe test will be used to determine equal variance. If the data are determined to be normally distributed and equal variance is observed between the groups, a repeated measures analysis of variance test will be used to detect between-group and within-group differences. If normality cannot be established or unequal variance is observed within the data, the Friedman test will be used to detect between-group and within-group differences. If the data are nonnormal with unequal variance, a Box-Cox transformation will be performed to obtain equal variances. For all tests, statistical significance will be set at *P*<.05.

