#### Power

This study was designed as a feasibility study for investigating the feasibility of a student-run initiative to reduce loneliness in older adults. A component of this study will be understanding recruitment and retention, which may have significant variability in our sample size. Based on previous studies on interventions to reduce loneliness in older adults, with an effect size of approximately 0.2 and alpha of .05 and 80% power, we expect our sample size to be 196 [43,50-54]. Accounting for attrition rates in other intergenerational programs would be approximately 10%, and the sample size would be 216 [20,55,56]. Since the nature of this study is a feasibility study, which we aim to use to guide a future randomized controlled trial, this feasibility trial is not registered.

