### Limitations

Obtaining a sufficiently large sample to observe statistical significance for the measures used is anticipated to be a challenge, as resource limitations necessitate that this study is only run at 1 location. Should additional funding be secured, there is a potential for this study to be run at multiple sites.

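### The Power section claims 80% power with 196 participants (216 after attrition) as this study's sample size, but about 20 are planned and efficacy is still tested at P<.05

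*Protocol article*

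**What the plan says.** Two sizes are given for one study.

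- Protocol article, Power: "with an effect size of approximately 0.2 and alpha of .05 and 80% power, we expect our sample size to be 196". Attrition is then added: "Accounting for attrition rates in other intergenerational programs would be approximately 10%, and the sample size would be 216". The section opens by calling the study a feasibility study. It mentions a future randomized trial only afterwards, when explaining why this one is not registered.
- Protocol article, Participant Recruitment: "We expected to enroll approximately 20 participants, 10 in each condition". Eight had been enrolled when the study was halted.

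The efficacy outcomes hold the primary position. Outcomes states: "The primary outcomes of this study are loneliness and depression". The last paragraph of the Introduction hypothesizes that the intervention reduces both. Under Statistical Analysis, Primary Outcomes specifies a repeated-measures approach to the weekly scores and adds "For all tests, statistical significance will be set at" P<.05. Enrolment, adherence and attrition are listed separately as feasibility outcomes.

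Limitations acknowledges the difficulty: "Obtaining a sufficiently large sample to observe statistical significance for the measures used is anticipated to be a challenge".

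**The concern.** The planned and calculated sizes differ about tenfold (196/20 = 9.8), and the text attaches 80% power to the larger one as this study's own number. A reader could credit the efficacy tests with power that the design does not have. A null result is then likely even if the programme works as assumed, and it could be taken as evidence of no effect. In a single between-arm comparison, a significant result would require an observed difference near 0.94 SD, well above the effect assumed in planning. What the study can usefully estimate for planning the next trial (recruitment, adherence, attrition) has no stated precision.

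**Working it through.** **Inputs from the article.** Effect size about 0.2, type not named; "alpha of .05 and 80% power"; 196, not said to be total or per arm; 10% attrition giving 216 (all from Power). About 20 participants, 10 per arm (Participant Recruitment). 1:1 allocation (Randomization and Blinding).

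**Assumptions.** Two-sided primary tests, because sidedness is not stated for them. 196 is read as a total. The correlation between weekly scores is not given; 0.3 to 0.9 is used.

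**1. Reproducing 196.** With z(0.975) + z(0.80) = 1.960 + 0.842 = 2.802, the square is 7.849.

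- Two arms, Cohen's d = 0.2: n per arm = 2 × 7.849 / 0.2² = 392.4, so 393 per arm and 786 in total. This is not 196.
- Two arms, Cohen's f = 0.2, which equals d = 0.4: n per arm = 2 × 7.849 / 0.4² = 98.1, so 99 per arm and 198 in total. This reproduces 196 closely.
- One-sample or paired change of 0.2 SD: n = 7.849 / 0.2² = 196.2. This also reproduces 196, but it is not a comparison between arms.

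The figure 216 is 196 × 1.10 = 215.6. Dividing by 0.9 gives 218, a trivial difference.

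**2. Power of a single between-arm comparison (noncentral t, two-sided .05).**

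| Size | d = 0.2 | d = 0.4 (f = 0.2) |
|---|---|---|
| 196 in total (98 per arm) | 29% | 80% |
| 20 in total (10 per arm) | 7.1% | 13.5% |
| 9 per arm, after 10% loss | 6.8% | 12.6% |

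A cross-check that does not need the effect-size type: if 196 in total gives 80% power, the noncentrality at 20 is 2.80 × √(20/196) = 0.895. Power is then about Φ(0.895 − 1.960) = 14%.

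**3. Using the weekly scores.** Averaging m = 8 scores with common correlation ρ multiplies the variance by (1 + 7ρ)/8.

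- ρ = 0.3: factor 0.3875. The effective d rises from 0.2 to 0.321 (power 10%) or from 0.4 to 0.643 (power 27%).
- ρ = 0.9: factor 0.9125. The effective d is 0.209 (power 7%) or 0.419 (power 14%).

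**4. Group-by-time test.** Its power needs the correlation and an interaction effect size, and neither is given. As an illustration only, with 20 participants, 8 assessments, sphericity and ρ = 0.5, the noncentrality is f² × 20 × 8 / 0.5. That is 3.2 for f = 0.1 (power about 19%) and 12.8 for f = 0.2 (power about 72%). No figure can be derived from the article for this test.

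**5. What 10 per arm can show.**

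- Difference detectable with 80% power in a single comparison: 1.32 SD (1.41 SD with 9 per arm).
- Half-width of the 95% confidence interval for an arm difference in a single score: 2.101 × √(2/10) = 2.101 × 0.447 = 0.94 SD.
- Attrition, if 2 of 20 are lost: exact 95% interval 1% to 32%.

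**The case against.** The strongest reply is that this is openly a feasibility trial. The abstract, Study Design and Power all say so, Power warns that recruitment and retention may vary, and Limitations concedes that significance will be hard to reach. A sample of 20 is therefore not an error in itself, and that stands. The disclosure does not, however, say which trial 196/216 belongs to, and it leaves the significance tests on the primary outcomes in place.

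Several stronger readings are tempting but not supported.

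- **Power is roughly 7%.** That holds only for Cohen's d = 0.2 in one two-sided comparison, and on that reading 196 in total would not give 80% either. The article does not name the effect-size type, and the planned analysis is repeated measures.
- **A null result is almost certain.** At 14% power per test, the chance of at least one significant primary result is up to 1 − 0.86² = 26% if the two tests are independent; at 27% it is up to 1 − 0.73² = 47%.
- **196 is a miscalculation.** It is essentially right if f = 0.2 was meant.
- **Feasibility is ranked below the secondary outcomes.** It has its own heading, with no stated rank.
- **Two primaries inflate the false-positive rate.** This depends on whether either one suffices. The hypothesis names both outcomes, and multiplicity rules are commonly left to an analysis plan.

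**Conclusion.** The point holds in this limited form: the article states 80% power for a size about ten times the one planned, calls it the study's own sample size, and does not reconcile the two. With 20 participants, a single between-arm comparison has about 7% power (d = 0.2) to 14% (f = 0.2). Averaging the weekly scores gives at most about 27% for correlations of 0.3 to 0.9. These figures assume two-sided tests and 196 as a total; the correlation range is an assumption, and power for the group-by-time test is unknown. The defect is not the small sample. It is the unreconciled power statement beside primary efficacy outcomes tested at P<.05.

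**What to change.** Before the halted trial restarts, revise the text as follows.

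- State about 20 (10 per arm) as this trial's size, say that it is not powered for efficacy, and give its precision: a 95% interval half-width of about 0.94 SD for an arm difference in a single score, and, for example, 1% to 32% for attrition if 2 of 20 are lost.
- State that 196/216 belongs to the future trial. Name the effect-size type and say whether 196 is total or per arm. If Cohen's d between arms is meant, recompute (about 393 per arm before attrition).
- Report the UCLA and CES-D results as arm differences with 95% confidence intervals, without a significance-based efficacy claim.
- Present enrolment, adherence and attrition as the outcomes that this trial is sized to inform.

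The cost is protocol wording and a more modest efficacy claim. Recruitment and data collection are unchanged.

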#### Student Recruitment

The study team will consist of 10 students from the University of Waterloo who are volunteers in the enTECH Computer Club. Student volunteers were recruited through school club advertisements, course announcements, and through social media. Student volunteers were interviewed and trained to provide technology education through in-house lesson plans and simulations.

### enTECH Intervention and Study Procedure

After obtaining informed consent, demographic information will be collected (Multimedia Appendix 6) and participants will be randomized as described above. The intervention outline is described below and detailed in the study flow chart of Figure 1.

*Week 0*: Members of the study team will conduct semistructured interviews with participants (Multimedia Appendix 7) and complete the Computer Proficiency Questionnaire-12 (CPQ-12) and the Older People’s Quality of Life-Brief version (OPQOL-Brief) questionnaire, which will be measured before and after the study period.

*Weeks 1-7:* Participants in the intervention group will complete the enTECH program. Trained enTECH volunteers will help older adults use either our laptops or participants’ own technology systems to email their family members. These sessions will take place in group settings in a public area in the long-term care facility accessible to all participants. Both the Center for Epidemiologic Studies Depression scale (CES-D) and the UCLA (University of California, Los Angeles) Loneliness Scale (version 3) will be measured each week in the intervention and control groups.

*Week 8:* Participants in both groups will complete their final session of the intervention, and they will then be asked to complete the CPQ-12, the OPQOL-Brief, the CES-D, and the UCLA loneliness scale. Participants in the intervention group will also be invited to complete a second interview discussing their experiences using technology to communicate with a family member (Multimedia Appendix 8).

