### Randomization and Blinding

After the consenting process, participants will be randomized to either the intervention or the control group by using a computer-generated allocation sequence in a 1:1 ratio. If randomized to the intervention group, researchers will work with the participants to obtain a family member’s email address for use in the study. Owing to the nature of the study, participants cannot be blinded to allocation. Two separate research teams will facilitate the study. The clinical team will be carrying out the intervention, while the research team will be conducting the interviews and administering the scales. In order to maintain participant confidentiality and anonymity to the interviewers, participants will be assigned a participant ID number via the allocation sequence described above. This number will be known to both the clinical team and the research team; however, the research team will not be able to see the participants in the intervention group or those in the control group. When data are entered into the computer, the data will be associated with the participant IDs alone.

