#### Secondary Outcomes

The OPQOL-Brief and the CPQ-12 will be analyzed by comparing changes in the scores between the intervention group and the control group. The normality of the data will be assessed using the Shapiro-Wilk test, and equality of the variances between the groups will be assessed via a Q-Q plot and the Brown-Forsythe test. The differences between prestudy and poststudy period assessments in the intervention and control groups will be assessed using pooled variances and a one-sided *t* test. If normality cannot be established or unequal variance is observed within the data, a Q-Q plot will be used to determine the appropriate test (eg, Sign test, Wilcoxon-Signed Rank Test, or Wilcoxon Rank-Sum Test). For all tests, statistical significance will be set at *P*<.05. Quantitative feasibility outcomes (eg, adherence and attrition) will be reported as descriptive data and compared using a one-sided *t* test or a nonparametric equivalent (Mann-Whitney *U* test). All evaluation outcomes will be integrated in a joint display.

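### Randomisation is placed before the Week 0 assessments in an unblinded trial, so the baselines for the two secondary scales can be given with knowledge of the arm

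*Protocol article*

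**What the plan says.** The order of steps is given twice in the Methods, and the two statements agree.

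- **Randomization and Blinding:** "After the consenting process, participants will be randomized to either the intervention or the control group". The same section states: "Owing to the nature of the study, participants cannot be blinded to allocation". It then describes a step for one arm only: "If randomized to the intervention group, researchers will work with the participants to obtain a family member’s email address for use in the study".
- **enTECH Intervention and Study Procedure:** here the sequence is set out as "After obtaining informed consent, demographic information will be collected (Multimedia Appendix 6) and participants will be randomized as described above". Next comes the weekly outline, which opens with Week 0 and holds there the semistructured interview, the CPQ-12 and the OPQOL-Brief.

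For the analysis, the Secondary Outcomes part of the Statistical Analysis section says: "The OPQOL-Brief and the CPQ-12 will be analyzed by comparing changes in the scores between the intervention group and the control group". It names a one-sided t test with pooled variance.

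The Randomization and Blinding section also describes one safeguard. A research team separate from the team delivering the programme conducts the interviews and administers the scales, and is meant not to know who is in which group.

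**The concern.** A baseline serves as a reference point because allocation cannot have influenced it. Here the demographics are collected before randomisation and the scales after it. A resident who knows the arm may answer Week 0 differently. For example, someone about to be taught may rate their computer skill lower, and someone disappointed at being a control may rate their quality of life lower. When the analysis subtracts that baseline, the reaction to allocation can appear as a treatment effect or can hide one.

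Two lesser consequences follow from the same order. A resident who leaves after randomisation but before Week 0 has no baseline and so no change score, which fits poorly with the intention-to-treat commitment in the Statistical Analysis section. The pre-programme interview, meant to describe how residents socialise before the programme, may also be coloured by the allocation.

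**Working it through.** The plan states no figure on this point, so the check is one of sequence, followed by an illustration.

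**Sequence.**
1. Randomisation follows consent and demographics and precedes Week 0 (both sections agree).
2. Participants are not blinded.
3. No statement in the text places Week 0 before randomisation or conceals the allocation until Week 0 is done. Figure 1, the flow chart, is not available here.
4. The CPQ-12 and OPQOL-Brief are Likert questionnaires answered by the participant. Masking the person who administers them does not affect what the respondent knows.

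**Effect on the change-score contrast.** Let τ be the true effect on change. Let b0 and b8 be the reporting shifts due to knowing the arm (intervention minus control) at Week 0 and Week 8.

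- Baseline taken after disclosure: expected contrast = τ + b8 − b0.
- Baseline taken before allocation: expected contrast = τ + b8.

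The current order therefore adds the term −b0. If the shift has gone by Week 8 (b8 = 0), the bias equals −b0 in full. If it persists unchanged (b8 = b0), it cancels. The two examples above push in opposite directions. Lower skill ratings in the intervention arm make b0 negative and inflate the effect. Lower quality-of-life ratings in the control arm make b0 positive and mask it.

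**Illustration.** From the Protocol article: about 10 per arm, one-sided t test with pooled variance, significance at .05. Assumed: no true effect; equal SDs at both times; a test directed towards benefit; pre-post correlation ρ; and a shift of b SD at Week 0 only, in the direction that inflates apparent improvement.

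- SD of change = √(2(1 − ρ)). With ρ = 0.5 this is 1.
- Noncentrality = b / (SD of change × √(2/10)). With b = 0.2 and ρ = 0.5 this is 0.2 / 0.447 = 0.447, on 18 degrees of freedom.

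| Assumed shift b (SD), ρ = 0.5 | False-positive rate, favourable direction | Opposite direction |
|---|---|---|
| 0 | 0.050 | 0.050 |
| 0.1 | 0.076 | 0.031 |
| 0.2 | 0.112 | 0.019 |
| 0.3 | 0.159 | 0.011 |
| 0.5 | 0.285 | 0.003 |

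With b = 0.2, the favourable-direction rate is 0.100 at ρ = 0.3 and 0.138 at ρ = 0.7. The documents give no size or direction for b, so the table shows sensitivity and is not an estimate.

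**The case against.** Several points on the other side carry weight.

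- **Disclosure before Week 0 is inferred.** Being unable to blind participants does not say when they learn their arm. The step to obtain a relative's email address is not dated. The Participant Recruitment section offers options for family contact after consent without limiting them to one arm, so it is unclear whether this contact work reveals the allocation. This stands. The defect is that the text permits disclosure before Week 0, not that it proves it.
- **A persistent shift cancels.** This also stands, as the algebra shows. A reader might infer that any Week 0 shift passes in full into the estimate, but that holds only for the part absent at Week 8. Cancellation depends on the two shifts being equal, which the design cannot ensure.
- **The reach is limited.** The change-score effect concerns two secondary scales in a feasibility trial expecting about 20 participants. The primary scales are not listed at Week 0. The interviews are analysed thematically and only the intervention arm is interviewed afterwards, so there is no between-arm change in interview data to bias.
- **Masked assessors.** This is a real but partial safeguard, because it does not affect what the respondent knows.

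Two stronger readings are tempting and unsupported. Recruitment opened in November 2019 and the intervention began in February 2020, so a reader might infer a gap of about three months between randomisation and the programme. No individual consent or randomisation is dated, so that interval is only a ceiling. A reader might also set a shift of 0.1 to 0.2 SD against the effect size of 0.2 in the Power section and call it half or all of the expected effect. The 0.2 comes from studies of loneliness, not from these two scales, and the shift is assumed, so the ratio carries no evidential weight.

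**Conclusion.** The ordering defect holds. As written, the Week 0 CPQ-12, OPQOL-Brief and interview follow randomisation in an unblinded trial, and nothing in the text prevents them from being answered with knowledge of the arm. The between-arm comparison of change in the two secondary scales is exposed to bias from any allocation-driven shift that does not last to Week 8. Size and direction are unknown. The illustrated error rates depend on the assumed shift and correlation. Possible loss between randomisation and Week 0, and colouring of the first interview, are further consequences that are plausible but not shown to have occurred.

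This should be fixed for the secondary outcomes. It does not by itself undermine the feasibility aims or the primary scales. It is worth correcting now because the trial is halted, is due to restart, and is meant to guide a future randomised trial.

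**What to change.** For participants enrolled at restart, reword the Randomization and Blinding section and the enTECH Intervention and Study Procedure section so that the order is consent, demographics, all Week 0 assessments, then randomisation. If randomisation has to come earlier for practical reasons, state that the allocation is not disclosed, and that no arm-specific step such as obtaining the relative's email address begins, until Week 0 is complete.

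For the 8 participants already enrolled, rewording cannot undo the order. Report for each whether Week 0 came before or after the allocation was known.

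State as a limitation that self-report at Week 8 remains unblinded, since the reordering leaves that source of bias untouched.

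The cost is protocol wording, a swap of two steps, and one extra item reported for the 8 participants. No extra visits, staff or participants are needed.

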**Methods:**

This study is a randomized, mixed-methods, feasibility trial with 2 conditions. Older adults in the intervention condition will receive 1 hour of weekly technological assistance to send an email to a family member, for 8 weeks, with the assistance of a volunteer. Participants in the control condition will not receive any intervention. The primary outcomes are loneliness, measured using the University of California, Los Angeles Loneliness Scale, and depression, measured using the Center for Epidemiologic Studies Depression scale, both of which are measured weekly. Secondary outcomes are quality of life, as assessed using the Older People’s Quality of Life-Brief version, and technological literacy, evaluated using the Computer Proficiency Questionnaire-12, both of which will be administered before and after the intervention. Semistructured interviews will be completed before and after the intervention to assess participants’ social connectedness, familiarity with technology, and their experience with the intervention. The study will be completed in a long-term care facility in Southwestern Ontario, Canada. Significance was set at *P*<.05.

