This study is being conducted to determine the feasibility and effects of the educational program of enTECH for older adults on the levels of loneliness and depression reported by older adults. We hypothesize that our intervention will reduce loneliness and depression in older adults.

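### The two primary outcomes, loneliness and depression, are not scheduled at Week 0, so the text does not secure an untreated baseline for either

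*Protocol article*

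**What the plan says.** The Protocol article, section enTECH Intervention and Study Procedure, assigns instruments week by week:

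- **Week 0:** a semistructured interview; participants also "complete the Computer Proficiency Questionnaire-12 (CPQ-12") and the "OPQOL-Brief) questionnaire, which will be measured before and after the study period". Neither the CES-D nor the UCLA scale is named.
- **Weeks 1-7:** "Participants in the intervention group will complete the enTECH program". Under the same entry, the CES-D and the UCLA "Loneliness Scale (version 3) will be measured each week in the intervention and control groups".
- **Week 8:** after the final session, "they will then be asked to complete the CPQ-12, the OPQOL-Brief, the CES-D, and the UCLA loneliness scale".

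The abstract (Methods) makes the same split. Of the primary outcomes it says "both of which are measured weekly", while it places the secondary outcomes before and after the intervention. The Introduction states the aim as a reduction: "We hypothesize that our intervention will reduce loneliness and depression in older adults". The Primary Outcomes part of the Statistical Analysis section plans a repeated measures analysis of variance, or a Friedman test, on the weekly scores.

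Randomization and Blinding places randomisation after consent. The procedure section puts it after consent and demographics, and describes it ahead of Week 0.

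**The concern.** A hypothesis of reduction is most directly tested against a score taken before any treatment. As listed, the secondary outcomes have such a score and the primary outcomes do not. The first primary-outcome value falls in the week in which sessions start, and its order relative to the first session is left open.

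Two things are at stake. If the Week 1 value is already treated and serves as the baseline, part of the effect may be removed from the estimate. If no baseline is used, the arms are compared without adjustment in a trial expecting about 10 participants per arm, which gives up precision. The trial is also meant to guide a later randomised trial. Without an untreated score it cannot reliably supply the baseline correlation or the SD of change needed to plan that trial.

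**Working it through.** **1. The schedule.** The plan attaches no figure to this point, so the check begins with the text.

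| Instrument | Role | Week 0 | Weeks 1-7 | Week 8 |
|---|---|---|---|---|
| CPQ-12 | secondary | yes | – | yes |
| OPQOL-Brief | secondary | yes | – | yes |
| UCLA | primary | not listed | weekly | yes |
| CES-D | primary | not listed | weekly | yes |

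The procedure section and the abstract agree, so this does not look like a slip in one place. Order within a week is given only for Week 8, where the scales follow the session. Nothing states the order in Week 1.

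**2. Chance difference at baseline.** Inputs: 10 per arm (Participant Recruitment) and an effect of 0.2 (Power), read here as a standardised mean difference, which is an assumption.

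- SD of the difference between arm means = √(2/10) = 0.447 SD.
- P(|difference| > 0.2) = 2 × [1 − Φ(0.2/0.447)] = 0.65.

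This describes noise that a baseline covariate could partly remove. It is not bias, and the standard error of an unadjusted comparison already reflects it.

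**3. Value of an untreated baseline as covariate.** The baseline-to-follow-up correlation r is assumed, since the documents give none. For one follow-up score the variance factor is 1 − r². The difference detectable with 80% power at two-sided .05 and 10 per arm is (1.960 + 0.842) × √(2/10 × (1 − r²)).

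| r (assumed) | 1 − r² | Detectable difference |
|---|---|---|
| no baseline | 1.00 | 1.25 SD |
| 0.5 | 0.75 | 1.09 SD |
| 0.7 | 0.51 | 0.89 SD |
| 0.8 | 0.36 | 0.75 SD |

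These factors apply to a single follow-up score. The gain for an analysis of eight weekly scores would differ.

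**4. Week 1 as baseline when it is already treated.** Suppose a share f of the final effect is present at the Week 1 measurement (assumed). A change score from Week 1 keeps 1 − f of the effect, and the required sample size grows by 1/(1 − f)².

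| f (assumed) | 0.2 becomes | Sample size factor |
|---|---|---|
| 12.5% | 0.175 | 1.31 |
| 25% | 0.15 | 1.78 |
| 50% | 0.10 | 4.0 |

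If Week 1 enters as a covariate instead, only its regression slope times the early effect is removed, so the loss is smaller when the slope is below 1.

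**The case against.** A reader might infer that the trial has no pre-intervention value for loneliness or depression and cannot measure or adjust for change. The documents do not support either statement.

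- The Week 1 scales could precede the first session, in which case they are a baseline. The CES-D also asks about the past week, so an early Week 1 score could cover untreated time.
- The legend of Figure 1 includes both scales, and the figure could not be checked. It may place them at Week 0.
- Weekly scores in both arms from Week 1 to Week 8 allow change from Week 1 and a group-by-time comparison. Randomisation keeps the comparison between arms valid without any baseline.
- The 65% figure is correct arithmetic but measures imprecision. Its 0.2 benchmark belongs to the sample size calculation for a much larger study, and even with adjustment the detectable difference at 10 per arm stays several times 0.2.
- This is a feasibility trial whose authors expect too small a sample for significance. Naming a baseline covariate is commonly left to an analysis plan.

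All of this stands, and it limits the point. It does not remove it. Which instruments are given at Week 0 is a matter of the visit schedule, which the article states in detail and consistently. An analysis plan cannot adjust for a score that was not collected, and the text nowhere ensures that it will be.

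**Conclusion.** The point holds in a limited form. Followed as written, the schedule gives both secondary outcomes a pre-intervention score and secures none for the primary outcomes. What is at risk is change from an untreated state and the precision from adjusting for it; the validity of the randomised comparison is not in question. The precision at stake is a variance factor of 0.75 to 0.36 for a single follow-up score, under an assumed correlation of 0.5 to 0.8. The loss from using a treated Week 1 baseline depends on how much effect one session produces, about which the documents say nothing.

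This should be fixed before the trial restarts, but it is not fatal. Confidence is moderate because Figure 1 could not be seen and the Week 1 order is unstated. If the figure places the scales at Week 0, the remaining task is to reconcile text and figure.

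**What to change.** Administer the UCLA scale and the CES-D to both arms before the first session, and say so in the procedure section, the abstract and Figure 1. There are two places for this:

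- **Preferred:** at the consent and demographics contact, before randomisation. Participants cannot be blinded, so this keeps knowledge of allocation out of the baseline answers.
- **Otherwise:** at the existing Week 0 contact. In the order described this falls after randomisation, so Week 0 cannot also count as pre-randomisation unless one of the two is moved.

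Name that score as the baseline covariate in the primary repeated-measures analysis. The Friedman fallback takes no covariate, so the plan should also say how the baseline enters if that route is used.

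The cost is two more 20-item questionnaires per participant and a small ethics amendment. The trial is halted and needs ethics approval to resume, so the amendment can go with that request. A baseline that is not collected cannot be recovered later.
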